## Abstract

**Introduction and Aim:**

Radial artery approach angiography is the current gold standard for coronary status diagnostics and eventual percutaneous revascularization (PCI). Currently, application of adequate, patent hemostasis based physical torniquets are used for puncture site control, to avoid bleeding, radial artery occlusion and damage (RAO and RAD). The Radial Artery Puncture Hemostasis Evaluation (RAPHE) is a prospective, randomized, multicenter clinical trial designed to investigate new, simplified techniques of radial artery hemostasis utilizing physical compression free methods.

**Methods and Results:**

The RAPHE study has been designed to evaluate the efficacy and safety of two non-compression based radial artery hemostasis methods: a 100% chitosan bioactive hemostatic dressing and a purpose-built radial potassium-ferrate based topical hemostasis disc. These devices will be investigated in a standalone configuration. Control group is a standard pneumatic airbladder-based compression device. A total of 600 patients will be enrolled in a three-way randomization (1:1:1) with two study and one control groups. Safety and efficacy endpoints are RAO, puncture site hematoma formation and RAD respectively, consisting of dissection, (pseudo)aneurism and/or fistula formation, measured post-procedure and at sixty days.

**Conclusion:**

The results from this trial will provide valuable information on new, simplified methods of radial artery hemostasis options and possibly simplify post-puncture management of patients.

**Clinical Trial Registration:**

[www.ClinicalTrials.gov], identifier [NCT04857385].

## Introduction

Transradial artery approach (TRA) coronary angiography and clinically driven percutaneous revascularization (PCI) has evolved into the worldwide standard in the past two decades. It has several benefits over the classical femoral approach including decreased mortality, less clinically significant bleeding, earlier patient mobilization, along with reduced hospital costs (1, 2) and is also preferred by most healthcare recipients. Radial artery use for increasingly complex coronary procedures have widened over the past years with even complex, high-risk rotational atherectomy based PCI successfully undertaken from a TRA, utilizing large bore guiding catheters. Bilateral use of the TRA has also been reported, in instances where additional entry points are required, as used in chronic total occlusion PCI. TRA is, however, not without its hindrances. Radial artery occlusion (RAO) and radial artery damage (RAD), encompassing vessel dissection, (pseudo)aneurism and eventual fistula formation are important associated phenomena accompanying TRA. Both findings were described in first ever publication reporting on TRA (3). Published meta-analysis research shows, that RAO frequencies vary on a large scale from < 1% all the way to 33% (4). Literature on the frequency and modality of RAD is less established, with vague data hinting at the fact that radial artery pseudoaneurysm and fistula formation occur seldom after TRA < 1% (5–8).

Furthermore, state-of-the-art hemostasis of a radial puncture site involves mechanical compression devices (MCD), (mainly using either a pneumatic balloon/airbladder or semiglobular compression rod) depending on various forms of so-called patent hemostasis (PH). To achieve this efficient and safe ipsilateral blood flow without puncture site bleeding a pulse oximeter is placed on the thumb of patients with simultaneous compression of the ulnar artery to eliminate retrograde flow through the palmar arches. After this torniquet pressure is gradually decreased and titrated until a signal on the oximeter is verified, demonstrating blood flow. This method assures, that blood flows though the punctured artery in an anterograde fashion yet does extravasate through the puncture site. This decrease in pressure must be performed every 10–20 minutes and always verified via the pulse oximeter. Streamlined PH methods have proven superior to fixed time, fixed pressure torniquet options (9–11). However, achieving any form of PH requires significant human resources and increased attention, especially during the initial 30 min after torniquet application. In higher volume catheterization laboratories one or more dedicated nurses must be allocated to ensure PH procedures are followed. If the required measures are not met to a full extent, that may compromise the patency procedure and lead to increased safety and efficacy concerns.

In recent years, development of non-compression based, hemostasis devices have emerged containing various, biological and/or chemical hemostatic elements. These achieve hemostasis without the need for long term pressure on the puncture sight. One of the two main products is the linear polysaccharide chitosan which acts as a bioactive, temporary seal to any bleeding wound (12, 13). Chitosan based bioactive techniques have been utilized in conjunction with MCDs to shorten torniquet times (14), leading to a significant decrease in pressure intervals (120 vs. 60/45/30 min). Also, in a recently published trial (15), standalone use of a catecholamine-chitosan based hemostatic device was compared to a pneumatic standard MCS. RAO rates were comparable, with 8.5 and 9.4% (*p* > 0.05) for the study and control device, respectively. Torniquet times were significantly shorter for the bioactive device (42 vs. 50 min, *p* < 0.01) with grade I and II bleeding frequencies also comparable (1.3 vs. 3.4%, *p* > 0.05). RAD rates were not reported.

Another device in clinical use incorporates a tailored hemostatic disc, with potassium-ferrate and a hydrophilic component as the active ingredients. The device rapidly dehydrates blood and causes prompt aggregation of proteins and cellular blood components, achieving quick hemostasis. Published data (16) underlines, that potassium-ferrate devices, when used in conjunction with a standard pneumatic MCD decrease hemostatic times (43 ± 14 min vs. 160 ± 43 min, *p* < 0.001), with no increase in bleeding complications (17.2 vs. 10.3%, *p* = 0.2) as compared to MCDs alone.

Standalone use (without mechanical augmentation) of these types of new bioactive hemostatic devices in TRA appears logical and could ease the required extensive manpower need of PH associated with MCDs and shorten compression times, yet sufficiently powered and purpose designed studies lack in this regard, which we seek to implement.

## Methods and Analysis

### Study Objectives and Definitions

The objective of the Radial Artery Puncture Hemostasis Evaluation (RAPHE) study is to evaluate the safety and efficacy of two novel, non-compression based, bioactive radial artery hemostasis devices: a 100% chitosan sponge bioactive dressing and the potassium-ferrate based topical discs applied in a standalone configuration. A pneumatic balloon inflatable MCD will serve as a well-established control.

RAPHE is a prospective, randomized, open-label, multicenter clinical trial, with three, high-volume university centers conducting the study, in Europe, Hungary.

### Endpoint Definitions and Hypothesis

The primary endpoint of the study will be a device oriented complex endpoint (DOCE). A complex endpoint has been defined, to assess hemostasis devices from both important clinical viewpoints: its efficacy in containing puncture site bleeding and its safety in terms of preserving radial artery patency and integrity.

DOCE will encompass the following: post-operative bleeding with visible hematoma formation after hemostasis device removal classified using the EASY methodology (17) (I), RAD, encompassing vessel dissection, (pseudo)aneurism and/or fistula formation (II) and RAO (III). These three parameters will be measured and quantified first at 24 hours after hemostasis device removal or at hospital discharge (whichever comes sooner), and again assessed at the 60-day follow-up visit.

Secondary endpoints will focus on human resource requirements and economics of devices. These include initial compression to achieve primary hemostasis (I), overall compression device usage time (II), and number of compression devices needed (III). Primary hemostasis is defined as the time in minutes, from application of the hemostasis device to the first successful decrease of the initial torniquet pressure, with success indicating no repeat bleeding from the puncture site. Overall compression time refers to total time of devices used as a hemostasis tool. In cases of acute bleeding following device use, a new, freshly opened tool may sometimes be required if the first one failed to contain bleeding. According to the RAPHE protocol, in case of initial device failure, a second, identical tool is to be utilized. If the second device also fails to contain puncture site bleeding, a bail-out hemostatic device will be employed. Thus, our last tertiary endpoint has been defined as follows: the need for a bailout compression method (I).

We hypothesize, that utilizing either of the novel bioactive devices in a standalone arrangement will prove clinically non-inferior to the other study and the control MCD, respectively. Furthermore, we assume, that the use of either one of the standalone bioactive devices will require less compression time, fewer human resources, and less management to successfully handle as compared to the MCD.

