### Randomization Procedure

Randomization of consented subjects may only take place in the absence of exclusion criteria after removal of the last coronary catheter, by a physician participating in the study. It will take place in a 1:1:1 ratio, independently for every site via a computer algorithm, between the: pneumatic balloon MCD, potassium-ferrate disc and 100% chitosan sponge devices.

The pneumatic balloon based MCD serving as the control device will be placed on the introducer sheath inflated with the provided syringe to 12 ml-s with simultaneous removal of the introducer. An additional 2 ml-s of air will be inflated in case of acute bleeding and repeated if needed. It will be removed via a simplified patent hemostasis protocol (24), in which, after achieving primary hemostasis, exact titration to true PH we will be achieved by removing 2–3 ml-s of air every 10–15 min using a pulse oximeter to verify patency. At 0 ml-s of remaining air the device will be removed. These procedures will be carried out by qualified nursing staff. Nurses have been instructed to strictly adhere to the PH protocols and to contact study physicians in case of any potential adverse events, especially those in conjunction with radial hemostasis.

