The standalone potassium ferrate disc and chitosan sponge devices will both be used in a similar way. They will be placed onto the junction of the intact skin and introducer and manually compressed. To aid better initial compression and prevent device adhesion to bloody surgical gloves, a ball gauze will be placed on the chitosan device. The potassium-ferrate disc will be compressed alone. During compression the introducer will be removed, allowing for a visible amount of blood to appear, which will activate the hemostatic properties in both devices. Strong manual compression will be held for 1 min. Devices will then be banded and held in place using self-adherent wraps as detailed above. Strong, occlusive fixation of the devices will be upheld for a total of 10 min, after which the self-adherent bond will be fully unwrapped until the hemostasis device is visible. By this time both devices will have activated and initiated the coagulation cascade and are firmly attached to the puncture site. If acute bleeding occurs, an additional, minimum 5 minutes of compression will be applied. If initial devices are no longer fit for use, a new similar one will be used. Re-wrapping will then occur without the application of relevant pressure, in a non-occlusive way. During this time the wrapping will only protect the hemostasis device from external influence (e.g., accidental dislodgement, slipping etc.). If the second randomized study device also fails to contain puncture site bleeding a bail-out device of choice shall be applied as per protocol, the choice of which is left to the discretion of the attending physician. After a period of 120 ± 15 min the self-adherent wrapping will be removed. The chitosan sponge device will also be removed using sterile saline irrigation. The potassium-ferrate disc will remain in place and removed by the patient after 24 hours post-procedure.

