RAPHE will focus on RAO, RAD and bleeding equally, from a device-oriented endpoint as all present clinical challenges influence quality of life of patients. With RAO, a conduit for further use is eliminated and clinical signs of upper extremity ischemia may present, necessitating surgical or endovascular treatments. Damage to the radial artery, clinically mostly manifesting as (pseudo)aneurysm and fistula formation can cause substantial pain/discomfort, paresthesia and even a palpable mass above the site of the puncture often causing a thrill in case of an arterio-venous fistula. These pathologies will likely require interventional methods or surgical repair to avoid chronic vascular conditions (5–8) and may cause a notable decrease in quality of life if left unchecked and/or untreated. Bleeding as the most common complication after TRA if serious may present as a significant or even critical issue. Thus a “perfect” compression device has a DOCE of zero per cent, as it causes no bleeding, RAO or RAD. In the RAPHE study we expect an overall DOCE rate, encompassing everything above of around 15% in all three arms of the trial.

The main goal of the study will be to determine, how standalone bioactive chitosan and/or potassium ferrate devices fare against the gold standard pneumatic airbladder based MCD. Besides clinically relevant safety and efficacy profiles, we will opt to also explore if fewer human resources are required to manage said bioactive devices. As per the RAPHE protocol, bioactive devices only require one adjustment, shortly after application and may require less overall compression time. Reducing the need for extensive human resource PH management and continuous MCD adjustments in high-volume centers is favorable, due to a multitude of factors. As bioactive devices do not require adjustments every 10–20 min, additional staff, managing strict PH protocols may be allocated elsewhere. In the RAPHE study we assume that patients randomized into one of the two investigational arms (potassium ferrate disc or chitosan sponge) will achieve primary hemostasis quicker and require less overall compression time as compared to MCD control subjects. From an economic point of view, the RAPHE trial will also be assessing the need of hemostasis units per patient in all three arms, and record if bail-out compression devices are needed. We have no convincing assumptions regarding these endpoints, due to a lack of prior reported data or in-house registries.

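### Time to primary hemostasis ends at a complete, scheduled release in the bioactive arms but at a first partial release in the control arm, so the planned superiority test of quicker hemostasis does not compare like with like

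*Protocol article*

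**What the plan says.** **Definition (Endpoint Definitions and Hypothesis).** One wording serves all three arms. The clock for primary hemostasis runs "from application of the hemostasis device to the first successful decrease of the initial torniquet pressure". A decrease counts only if it holds, "with success indicating no repeat bleeding from the puncture site".

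**Bioactive arms (Randomization Procedure).** "Strong manual compression will be held for 1 min"; the device is then banded. "Strong, occlusive fixation of the devices will be upheld for a total of 10 min, after which the self-adherent bond will be fully unwrapped". After that, "Re-wrapping will then occur without the application of relevant pressure, in a non-occlusive way". If the site bleeds on unwrapping, the clock is extended: "If acute bleeding occurs, an additional, minimum 5 minutes of compression will be applied".

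**Control arm (Randomization Procedure).** The bladder is filled to 12 ml, with 2 ml top-ups for acute bleeding. Air is then let out by "removing 2–3 ml-s of air every 10–15 min using a pulse oximeter to verify patency", and the device comes off at 0 ml. This section places the air removal after primary hemostasis has been achieved. It gives no clock time for the first removal.

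**Use of the endpoint.** The Statistical Analyses section tests secondary endpoints for superiority. The Discussion expects that bioactive patients "will achieve primary hemostasis quicker and require less overall compression time as compared to MCD control subjects".

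**The concern.** The same words describe two physical events. In the bioactive arms the absence of re-bleeding is judged with no relevant pressure on the artery. In the control arm it is judged with most of the air still in the bladder. The bioactive value is also largely set by the protocol: a patient treated as described cannot score below about 10–11 min, and all who do not re-bleed score about the same.

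The control definition is circular as well. The endpoint section defines primary hemostasis by the first successful decrease in pressure, while the procedure section starts decreasing pressure only once primary hemostasis has been reached. A nurse following both texts cannot tell which event to time-stamp.

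At stake is a headline secondary claim, that these devices achieve hemostasis faster. A significant result in either direction could reflect the timing of the first permitted release more than how well a device stops bleeding.

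**Working it through.** The article gives no expected value, sample size or power for this endpoint, so there is no stated figure to reproduce. The check is schedule arithmetic followed by simulation.

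**1. What stops the clock in each arm**

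| | Bioactive arms | MCD arm |
|---|---|---|
| First decrease | full unwrapping | 2–3 ml out of 12 ml |
| When | scheduled at 10 min (10 + 1 = 11 if manual compression is counted separately) | not stated |
| Pressure left | none of relevance | most of the air |
| If bleeding occurs | at least 5 min more, so 10 + 5 = 15 min or later | 2 ml top-up, no time given |

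The step from manual compression to banding at 1 min could also be read as a first decrease, which adds a further ambiguity.

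**2. Air left after the first MCD step** (before any top-up)

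- (12 − 3)/12 = 75%
- (12 − 2)/12 = 83%

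**3. How far the schedule alone decides the test**

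Assumptions: 200 per arm; bioactive release at 10 min, plus 5 min per re-bleed; an MCD re-bleed adds one more MCD interval; random scatter with SD 1 min; Mann-Whitney test at two-sided 5%; 500 repeats per row. The time of the first MCD step is **assumed**, so it is varied. The table shows how often one bioactive arm is declared quicker than the MCD, with the mean difference (bioactive minus MCD) in brackets.

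| Re-bleed rate, bioactive vs MCD | MCD step spread over 10–15 min | MCD step at 10 min | MCD step at 15 min |
|---|---|---|---|
| 5% vs 5% | 100% (−2.9 min) | 3.4% (−0.3) | 100% (−5.5) |
| 10% vs 10% | 100% (−3.4) | 4.2% (−0.6) | 100% (−6.1) |
| 20% vs 10% | 100% (−2.6) | 2.2% (+0.1) | 100% (−5.4) |
| 30% vs 10% | 100% (−1.8) | 0% (+1.0) | 100% (−4.5) |
| 40% vs 10% | 86% (−0.6) | 0% (+2.2) | 100% (−3.3) |

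As a check on the simulation, giving all arms the same schedule, the same extension and the same 10% re-bleed rate yields 2.4% for bioactive declared quicker and 5.2% for Kruskal-Wallis, which is nominal.

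**4. Sensitivity to counting the manual minute**

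Here the bioactive time is 11 min (SD 0.5), every patient succeeds at first release, and there are 1000 repeats.

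- MCD uniform over 10–15 min: bioactive quicker in 100%.
- MCD uniform over 10–12 min: about 3–4% in each direction.
- MCD at 10 min (SD 0.5): MCD quicker in 100%.

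The sign therefore turns on a time that the article does not give.

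**5. Time to the same physical state in all arms** (no relevant pressure)

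- Bioactive: 10–11 min.
- MCD, fastest: 12/3 = 4 steps × 10 min = 40 min.
- MCD, slowest: 12/2 = 6 steps × 15 min = 90 min.
- Gap: 40 − 11 = 29 min up to 90 − 10 = 80 min.

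These MCD times assume that the first step comes one interval after application. The gap is also set by the schedules.

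**The case against.** **Device performance does enter.** Success requires no repeat bleeding, and bleeding costs a bioactive patient at least 5 min. This stands. A reader might infer that the endpoint compares only schedules and says nothing about devices, and the article does not support that. It supports a result driven largely by schedule, since under the 10–15 min assumption a device that re-bleeds more often can still win.

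**The size rests on an unstated input.** The 10–15 min interval belongs to the titration after primary hemostasis and is not given as the time to it. This also stands. A reader might infer that significance in favour of the bioactive devices is almost certain. That follows only under the assumed 10–15 min first step and does not hold at 10 min.

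**The asymmetry can work against the bioactive devices.** Staying dry after complete release is a harder test than staying dry after a small step. This stands as a limit on direction. It does not make the arms comparable.

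**Residual air is not residual pressure.** No pressure–volume relation is given and top-ups change the starting volume, so 75–83% is a statement about air volume only.

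**The secondary endpoints concern staffing and cost.** Comparing regimens as delivered is legitimate for that purpose. It does not support a claim of quicker hemostasis.

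**The article is condensed.** The time of the first MCD decrease may well be in the full protocol, and its absence here is not the point. The article does fix the definition and both procedures, and those do not match.

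**Conclusion.** The point holds as a problem of comparability. One definition is applied to a complete release at a scheduled 10 min (about 11 with manual compression) in two arms and to a partial release in the third, and the control definition is circular between the two sections. The planned superiority comparison therefore depends largely on when each regimen permits the first release.

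Direction and size are not determined by the article. With equal re-bleeding, the chance of declaring the bioactive device quicker runs from about 3–4% (MCD step at 10 min, bioactive also at 10) to 100% (MCD step over 10–15 min). With the bioactive time at 11 min and the MCD at 10 min, the result reverses. All of these figures rest on the assumed first MCD step, the assumed scatter and 200 analysed per arm.

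The matter should be corrected, but it concerns one secondary endpoint and leaves the primary endpoint untouched. Which release schedule is appropriate is not judged here.

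**What to change.** 1. Reconcile Endpoint Definitions and Hypothesis with Randomization Procedure, so that each arm has one named event that stops the clock, and remove the circularity for the MCD. No release schedule needs to change.
2. Report the first-decrease time descriptively by arm, with no superiority claim of quicker hemostasis.
3. Compare instead the proportion of patients who reach the pressure-free state (bioactive: full unwrapping; MCD: 0 ml of air) with no re-bleeding, added compression, replacement device or bail-out.
4. Report time to the pressure-free state as a difference between regimens, and say that it too is set by schedule (about 10–11 min against 40–90 min). It aligns the physical state across arms but is no better as a superiority endpoint.

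**Cost.** Wording in the protocol and analysis plan. Patient Data Collection already has device times recorded to the minute, and device counts and bail-out are already endpoints. The team should confirm that the case report form also captures re-bleeding, MCD top-ups and added compression. One secondary endpoint loses its inferential claim, and the pressure-free time for the MCD coincides with device removal. The proportion is still reached at different times in the two regimens, so it too should be described as a regimen comparison.

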### Sample Size Calculation

Sample size calculation was carried out for non-inferiority studies following established guidelines (18, 19) with a significance level of 95% and a power of 80%. Although the best reported component of the DOCE, RAO rates range from < 1 to 33% (4), and it would be advisable to estimate sample size calculations for the worst-case scenario (i.e., 33%), however analyses of our own existing data regarding RAO and RAD (The RadPress trial—unpublished) deemed this value unreasonable for the centers involved. Therefore, we used a conservative 15% of the population rate for the DOCE for both intervention and control treatments. We allowed a 10% relative inferiority margin for the investigated treatments (20). The resulting sample size was 158 patients per arm. We also accounted for a potential 10% drop-out rate and factored in the uncertainty in true DOCE rates, and hence sample size estimates, and thus rounded the sample size to 200 patients per arm.

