### Statistical Analyses

Data analysis will be done on an intention to treat basis. Baseline patient and disease characteristics will be summarized with detailed descriptive statistics that entail mean, median, SE, SD, IQR and range for continuous variables, while for categorical variables absolute and relative frequencies will be reported. Hypothesis testing of the primary outcome will be done with Fisher’s exact test with a significance level of 95%. Univariate analyses of secondary endpoints will be carried out as superiority analyses with one-way ANOVA, Kruskal-Wallis test, or logistic regressions, depending on the outcome variable type and distribution. Multivariate analyses of secondary endpoints will entail using general or generalized hierarchical mixed effects models depending on variable type and distribution. All statistical analyses will be done in the R statistical environment (21).

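### Bail-out after two failed devices is not a primary event, so with unequal bail-out rates the non-inferiority result would describe device plus rescue rather than standalone use

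*Protocol article*

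**What the plan says.** All references are to the protocol article.

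- **Purpose of the primary endpoint** (Endpoint Definitions and Hypothesis): DOCE is to assess a device on "its efficacy in containing puncture site bleeding and its safety in terms of preserving radial artery patency and integrity".
- **Its components** (same section): "post-operative bleeding with visible hematoma formation after hemostasis device removal classified using the EASY methodology", RAD and RAO. They are measured at 24 hours or discharge, and again at 60 days.
- **Rescue** (same section): a failed device is replaced once by an identical one. Then: "If the second device also fails to contain puncture site bleeding, a bail-out hemostatic device will be employed". For the bioactive arms, the device-use text under Randomization Procedure lets the attending physician choose the bail-out device, and the control mechanical compression device (MCD) is not excluded.
- **Rank of rescue** (Endpoint Definitions and Hypothesis): "our last tertiary endpoint has been defined as follows: the need for a bailout compression method". The number of devices used is a secondary endpoint.
- **Hypothesis** (same section): "utilizing either of the novel bioactive devices in a standalone arrangement will prove clinically non-inferior". The Introduction explains the term: "Standalone use (without mechanical augmentation) of these types of new bioactive hemostatic devices in TRA appears logical".
- **Analysis set** (Statistical Analyses): "Data analysis will be done on an intention to treat basis".
- **Expected bail-out** (Discussion): the authors state that they have no convincing assumption for it.

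**The concern.** Bleeding through two assigned devices is the most direct failure of a hemostasis device, yet it falls outside the endpoint that is said to measure containment of bleeding. Such a patient is analysed in the randomised arm and counts as event-free unless a hematoma, RAD or RAO is found afterwards. A bioactive-arm patient rescued with the control MCD no longer had use without mechanical augmentation, but still contributes a success to the bioactive arm.

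The steps before bail-out also differ by arm (Randomization Procedure). The MCD can be given more air, repeatedly. A bioactive device gets at least 5 more minutes of compression and, if it is no longer usable, a replacement. Unequal bail-out rates are therefore possible.

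What is at stake is the meaning of a positive primary result. It could be reported as non-inferiority of a standalone device when it partly reflects what the rescue device achieved.

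**Working it through.** **1. The plan's own figure.** Sample Size Calculation gives 15% DOCE in both arms, 80% power and 158 patients per arm. Assuming a one-sided 5% level and an absolute margin of 10 points:

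n = (1.645 + 0.842)² × 2 × 0.15 × 0.85 / 0.10² = 157.7, rounded up to 158.

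This reproduces the stated number, so an absolute 10-point margin is used below. The article words it differently ("We allowed a 10% relative inferiority margin for the investigated treatments"). That is a separate issue and nothing here rests on it.

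**2. Inputs.**

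- From the document: 15% DOCE, applied here to patients without bail-out; 200 per arm less 10% drop-out = 180.
- Assumed, because the document gives no values: control bail-out c = 2%; bioactive bail-out f = 5% or 10%; DOCE rate among rescued patients q = 30%, 50% or 80%, the same in both arms.

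**3. Difference left outside DOCE.** Rescued patients without a DOCE event make up (1 − q) × bail-out rate of an arm. The difference between arms that DOCE does not count is (1 − q)(f − c), which is 0 when f = c.

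| q | f = 5% | f = 10% |
|---|---|---|
| 30% | 0.70 × 3 = 2.1 points | 0.70 × 8 = 5.6 points |
| 50% | 0.50 × 3 = 1.5 points | 0.50 × 8 = 4.0 points |
| 80% | 0.20 × 3 = 0.6 points | 0.20 × 8 = 1.6 points |

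**4. Effect on the conclusion.** The probability that the upper one-sided 95% limit lies below 10 points is Φ((0.10 − gap)/SE − 1.645), with unpooled SE and n = 180 per arm.

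*Bail-out counted as an event.* The event rate is b + (1 − b) × 0.15, where b is the bail-out rate: 16.7% at 2%, 19.25% at 5% and 23.5% at 10%.

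- 5% v 2%: gap 2.55 points, SE 4.05 points, probability 0.58.
- 10% v 2%: gap 6.8 points, SE 4.21 points, probability 0.19.

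*DOCE as written.* The gap is (q − 0.15)(f − c).

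| q | f = 5% | f = 10% |
|---|---|---|
| 30% | 0.80 | 0.74 |
| 50% | 0.74 | 0.57 |
| 80% | 0.65 | 0.32 |
| *Bail-out counted* | *0.58* | *0.19* |

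The contrast is wide at q = 30% and narrow at q = 80%. The more often rescued patients show a hematoma, RAD or RAO, the more DOCE registers the failure by itself.

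**5. Precision of the added analysis.** The 90% half-width is 1.645 × √(2p(1 − p)/180):

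- DOCE at 15%: 6.2 points.
- Bail-out counted, equal 2% bail-out (p = 16.7%): 6.5 points.
- Bail-out counted, equal 10% bail-out (p = 23.5%): 7.4 points.

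With truly equal arms, the upper limit would exceed 10 points by chance with probability 16% for DOCE, and 18% (2% bail-out) to 28% (10%) for the supportive analysis.

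Statistical Analyses names Fisher's exact test for the primary outcome. The figures above use a confidence limit against the margin.

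**The case against.** - **Supportive analyses belong in the statistical analysis plan, which is not shown.** This stands as far as it goes: the absence of such an analysis from the article is not the point. The point is how three elements that the article does fix (DOCE's components, the rank of bail-out and the standalone hypothesis) fit together.
- **Standalone may describe only how the assigned device is applied.** The rescue rule comes just before the hypothesis and applies to all arms, so the hypothesis may already include rescue. That reading is possible, and comparing strategies under intention to treat is legitimate. The result should then be labelled that way, because the Introduction ties the term to use without mechanical augmentation.
- **Device failure is already reported.** A reader might infer that failures are hidden. They are not: device count is a secondary endpoint and bail-out a tertiary one. They lie only outside the comparison that carries the non-inferiority claim.
- **No imbalance is shown.** A reader might infer that bioactive devices will need more rescue and that the trial is biased towards non-inferiority. The document gives neither direction nor size. Bail-out needs two successive failures; if these were independent, 10% bail-out would imply about 32% first-device failure (√0.10 = 0.316). The 10% case is an illustration, not a forecast.
- **Rescued patients may mostly have DOCE events anyway.** DOCE counts visible hematoma of any EASY class, so q could be high. This stands, and is why the range runs to 80%.
- **Bail-out is an open-label bedside decision, whereas the sonographic examiner is blinded.** This stands too. A composite that includes bail-out should not be the sole basis for judging standalone performance.

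**Conclusion.** The concern holds in conditional form. DOCE does not count failure of two assigned devices followed by rescue. If bail-out is more frequent with a bioactive device, the primary result describes the device strategy including rescue and does not by itself establish the standalone hypothesis. With equal bail-out rates, and the same DOCE rate among rescued patients in each arm, the comparison is unaffected.

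The size cannot be fixed from the document. Under the assumptions above, the difference outside DOCE is about 0.6 to 2.1 points at 5% v 2% bail-out and 1.6 to 5.6 points at 10% v 2%. The document does not support going further and calling the intention-to-treat comparison invalid, or saying that bail-out must become a primary event. This is worth correcting before data are seen, with medium confidence in its practical weight.

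**What to change.** In Statistical Analyses, prespecify one supportive intention-to-treat analysis of DOCE with bail-out counted as an event. Report its confidence interval beside the primary result, together with bail-out rates by arm. Attach no pass/fail gate, since the supportive limit would miss 10 points by chance in 18% to 28% of trials with equal arms.

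Describe the primary result as non-inferiority of the device strategy including rescue. Read standalone performance from the primary result, the supportive analysis and the bail-out rates together, and note that bail-out is decided at the bedside without blinding.

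DOCE, the primary test, the rescue procedure and the sample size stay as they are, so primary power does not change.

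The cost is a few sentences and one extra analysis of data already recorded. The downsides are a narrower label for the primary result, a somewhat wider supportive interval (90% half-width 6.5 to 7.4 points, against 6.2 for DOCE) and a possibly less favourable supportive result.
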